### Semi-structured interviews

To inform our evaluation of the feasibility, acceptability, and sustainability of our proposed intervention, at the end of study, we will conduct 30-min interviews with the participating multidisciplinary specialists to obtain their perceptions of participation, satisfaction, and potential barriers to sustained participation. Sustainability will be influenced by how clinic administrators perceive participating clinicians’ performance and clinician’s perceptions of the expert consultation model. Thus, we will conduct 30-min qualitative interviews with both clinicians and clinic administrators to assess perceptions of change in clinicians’ productivity, patient panel composition, quality of care for complex cases, and influence on peers in the same clinic.

### Learners

Monitoring and evaluation of the monthly interactive webinar and quarterly short courses will include information from registered learners, webinar attendance data, and post webinar surveys. The demographic data will include but will not be limited to identifiable information about a learner’s affiliated organization, city of practice, clinical area of expertise, and patient populations served. The monthly interactive webinar and quarterly short course registration and attendance data will be collected passively through Zoom and REDCap Cloud, UNM, and UoC’s registration software, respectively. The attendance data will measure how many sessions each learner attended and the amount of time they attended. The objectives of this data collection are (1) to support the provision of CME and (2) to document the reach of the educational component of this intervention.

Project ECHO UNM will offer instant CME, CNE, and CPE credits to learners at each monthly interactive webinar. Learners will obtain the credits by filling out a brief post webinar survey accessed through a link in the email announcement and entered in the Zoom Chat toward the end of each webinar. Learners will fill out a survey with a standard set of questions required for accreditation as well as additional questions identified by collaborators as essential for the purposes of the program. Since the survey is required to receive educational credits, it must be personally identified and is therefore not anonymous. The survey will remain open after the monthly interactive webinar for a short time. After learners complete the survey, they will receive a certificate via email. Project ECHO will utilize a REDCap online data collection system to collect survey data for all post-webinar surveys. After each webinar, a formal feedback report will be provided to include a summary of responses and comments by session, aggregate CME feedback, total credits awarded, and attendees by type.

The quarterly short course survey will mirror the monthly interactive webinar survey. Any learner who is not a part of the randomized controlled trial will be asked to give consent for follow-up surveys. The quarterly short course survey responses, registration information, and attendance data for learners will be shared in an aggregate follow-up report with FHCSD.

### Data collection and generation methods

Clinicians will generate data via self-reported survey, clinical encounters, and engagement in teleECHO sessions. Data will be captured and stored using REDCap Cloud and iEcho. Patients will generate data via self-reported survey and results of clinical encounters. Data will be captured and stored within the EHR/CMIS at FHCSD. Researchers will generate data from review of clinical encounters with EHR and teleECHO sessions. Data will be captured and stored within EHR/CMIS at FHCSD, REDCap Cloud, and iECHO.

In addition, semi-structured interviews will be conducted with clinicians, multidisciplinary specialists taking part in teleECHO sessions, and clinic directors at FHSCD. All 30-min interviews will be recorded and transcribed, and transcriptions will be stored and processed using N-Vivo (QSR International software) for qualitative analysis. Learners will generate data via self-reported demographic information when registering for the monthly ECHO sessions and/or quarterly asynchronous short courses. In addition, learners will generate data via a self-reported survey upon completion of the monthly ECHO session and/or quarterly asynchronous short courses. Each of the pathways for the collection/generation of data will have a corresponding standard operating procedure (SOP) that trained staff will follow to ensure data quality.

#### Data privacy, management, and quality assurance

This study has been determined to be no more than minimal risk, given that risks are not greater than those encountered in the context of delivery and receipt of medical care. Any potential spontaneously reported harms will be dealt with in alignment with the policies and procedures of the covered entity, FHCSD. All data generated by clinicians and patients will be gathered using digital tools that allow for programming of data fidelity checks (e.g., preset ranges of acceptable values, error notifications for unexpected values, summary of skipped measures). Trained members of the research team will systematically review data generated by clinicians and patients in order to identify any issues that may be addressable in a timely fashion after data are meant to be collected. Data generated by trained research staff through chart review and administrative extraction will undergo manual fidelity checks by an additional member of the research team who will evaluate the data for completeness and accuracy.

The confidentiality of clinician and patient data is a top priority for the research team. Any information obtained about clinicians and patients during this study will be treated as strictly confidential to the full extent permitted by applicable law and in accordance with HIPPA regulations. Only trained members of the research team will have access to patient identifiers and data collected. All members of the research team will be trained to ensure confidentiality and adherence to standardized procedures. All research staff directly involved with the collection and storage of research materials will complete CITI training and internal FHCSD HIPAA and data security training. In addition, the research study will comply with policies established by FHCSD’s Data Security Plans. To ensure confidentiality, a research code number will be assigned to each participant and information that may identify them. The research code numbers will only be provided to qualified study investigators. Files linking names and other identifying information to data will be electronically saved using technology that prevents unauthorized individuals from accessing and understanding it. If a participant’s information is printed, it will be kept locked and accessible only to certified research staff. When study results are published no personally identifying information (according to HIPAA guidelines) will be revealed. All data will be collected and managed using secure, password protected, web-based tools that allow for programming of data fidelity checks (e.g., preset ranges of acceptable values, error notifications for unexpected values, summary of skipped measures). All entities involved in the present research (FHCSD, UNM, UoC, Ata Health, and UW) have access to such tools, like REDCap. REDCap provides an intuitive interface for data entry, audit trails for tracking data manipulation and export procedures, automated export procedures for seamless data downloads to common statistical packages, and procedures for importing data from external sources. Trained research staff will systematically review data generated by clinicians and patients in order to identify any issues that may be addressable in a timely fashion after data are meant to be collected. Data generated by trained research staff through chart review and administrative extraction will undergo manual fidelity checks by an additional member of the research team who will evaluate the data for completeness and accuracy. The present study is not exceptionally large or long term, and no planned interim analyses for efficacy or futility will be conducted. Therefore, a Data Safety and Monitoring Board will not be appointed.

### Statistical analysis

Analyses will be based on the intention-to-treat principle. All patients will be analyzed in the condition to which the clinician to which they were assigned was randomized regardless of compliance or fidelity. A “per-protocol” secondary analysis will be considered if compliance or fidelity of clinicians is a concern. All tests of significance will be two-sided and a *p*-value of 0.05 will be considered statistically significant. Group comparisons will be conducted on all the measured baseline patient characteristics to identify potential systematic differences between patients in each study arm. Identified patient characteristics that are not balanced will be used as covariates in the subsequent modeling of the data. Potential differential attrition between the two study arms will be compared and adjusted for in analyses. Analyses of differences in outcomes at both the patient- and clinician-level will include a linear mixed model to compare change in outcomes from baseline to each post-baseline assessment between the randomized study arms. Fixed effects will include the study condition, assessment, study condition-by-assessment interaction, baseline measure, and any unbalanced covariates. Assessment will be treated as a categorical variable, and an unstructured variance–covariance structure will be used. Results will be reported as point estimates (mean differences between groups) and interval estimates (95% confidence intervals). An intervention effect will be concluded if the *p*-value for the study arm-by-assessment interaction contrast in the model at the final assessment is statistically significant. This approach uses all available data and is robust to data missing at random (MAR).

Changes over time among clinicians in the intervention condition will be analyzed using generalized estimating equation (GEE) models with an exchangeable correlation structure. Depending on the variable distribution, we will either use log-binomial or Poisson models. The GEE approaches allow us to examine differences in subgroups by first including interaction terms into the models. This will enable us to explore if the intervention differentially impacts subgroups of learners and care teams defined by a variety of variables of interest (e.g., age, sex, location, etc.). Similar longitudinal data analysis approaches will allow us to examine differences in outcomes between cohorts at FHCSD and UW. In order to investigate the time to uptake of specialist recommendations between cohorts, a Cox proportional-hazards model will be applied. In addition, Kaplan–Meier curves and log-rank tests will be performed.

Data from the semi-structured qualitative interviews will be transcribed verbatim, transcripts will be uploaded into N-Vivo (QSR International software) for qualitative analysis. We will use a three-phased thematic analysis technique to code the responses using deductive and inductive codes. Authentication of key themes will occur by discussion and consensus with the research team.

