**Methods:**

We aim to assess the effectiveness of a Long COVID and Fatiguing Illness Recovery Program (LC&FIRP) in a two-arm, single-blind, pragmatic, quality improvement, professional cluster, randomized controlled trial in which 20 consenting clinicians across primary care clinics in a Federally Qualified Health Center system in San Diego, CA, will be randomized at a ratio of 1:1 to either participate in (1) weekly multi-disciplinary team-based case consultation and peer-to-peer sharing of emerging best practices (i.e., teleECHO (Extension for Community Healthcare Outcomes)) with monthly interactive webinars and quarterly short courses or (2) monthly interactive webinars and quarterly short courses alone (a control group); 856 patients will be assigned to participating clinicians (42 patients per clinician). Patient outcomes will be evaluated according to the study arm of their respective clinicians. Quantitative and qualitative outcomes will be measured at 3- and 6-months post-baseline for clinicians and every 3-months post assignment to a participating clinician for patients. The primary patient outcome is change in physical function measured using the Patient-Reported Outcomes Measurement Information System (PROMIS)-29. Analyses of differences in outcomes at both the patient and clinician levels will include a linear mixed model to compare change in outcomes from baseline to each post-baseline assessment between the randomized study arms. A concurrent prospective cohort study will compare the LC&FIRP patient population to the population enrolled in a university health system. Longitudinal data analysis approaches will allow us to examine differences in outcomes between cohorts.

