### Study design

We will evaluate LC&FIRP using an effectiveness implementation hybrid type 2 design [16]. Specifically, we will conduct a two-arm, single-blind, pragmatic, quality improvement, professional cluster, randomized controlled trial in which 20 consenting clinicians across primary care clinics at FHCSD will be randomized at a ratio of 1:1 to either participate in (1) weekly teleECHO sessions with monthly interactive webinars and quarterly short courses or (2) monthly interactive webinars and quarterly short courses alone (a control group). All clinicians will have the option to receive Continuing Medical Education (CME) credit for the weekly teleECHO sessions and monthly interactive webinar. More details on the content of the weekly teleECHO sessions, monthly interactive webinars, and quarterly short courses are provided below. Clinicians will participate in LC&FIRP up to 37 months and throughout participation, 856 FHCSD patients diagnosed with PCC, ME/CFS, or other PIFI will be assigned to the participating clinicians (approximately 42 patients per clinician). Patient outcomes will be evaluated according to the study arm of their respective clinicians. Quantitative and qualitative outcomes will be measured at 3-, 6-, 9-,12-, 18-, 24-, and 30-months post-baseline for clinicians and for patients at 3-, 6-, 9-, and 12-months post assignment to a participating clinician. We will concurrently conduct a prospective cohort study to compare the two patient populations resulting from the randomized controlled trial with a third patient population resulting from enrollment at University of Washington’s Post-COVID Rehabilitation and Recovery Clinic (https://www.uwmedicine.org/specialties/post-covid-rehabilitation). An overview of the study period for clinicians and patients can be found in Table 1.

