#### Participants

The target for weekly teleECHO sessions, monthly interactive webinars, and quarterly short courses is licensed health care professionals. Therefore, the present research will include professional clusters that will consist of primary care physicians, physician assistants, and nurse practitioners at FHCSD caring for patients who have had persistent symptoms and a decline in health-related quality of life associated with PCC, ME/CFS, and/or other PIFI. A total of 20 clinicians (10 in each study arm) will be enrolled and throughout participation, 856 FHCSD patients diagnosed with PCC, ME/CFS, or other PIFI will be assigned to those participating clinicians (42 patients per clinician). In order to achieve a similarly sized sample of patients among cohorts in the proposed longitudinal cohort study, we will include 428 patients from the UW Medicine’s Post-COVID Telehealth Clinic who have been diagnosed with PCC, ME/CFS, and/or other PIFI.

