### Researchers

Researcher generated data will be collected by FHCSD staff supporting LC&FIRP through EHR chart review and survey data including clinical changes to practice, participation in interventions available, exposure to interventions, and patient experience. For all clinicians participating in the Randomized Control Trial, the changes to practice will be measured by the volume of total patient case load, volume of PCC and ME/CFS patient case load, and number of referrals made to specialists at the established intervals of 3-, 6-, 9-, 12-, 18-, and 30-months post baseline. For the 10 intervention clinician participants, assessment of changes to practice will include proportion of cases presented to a multidisciplinary specialist panel and number of specialist recommendations applied from case consultation. In addition, for the 10 intervention clinicians, we will measure the participation and exposure to topics in weekly teleECHO sessions, as well as participation in presenting case forms. For all 20 clinician participants, we will review participation in monthly interactive webinars and quarterly short courses and exposure to topics discussed in each, respectively. We will conduct an EHR chart review to measure the number of specialists seen by a patient and specialty types they were exposed to during their 12-month follow-up period. The objective of this data collection is to inform patient and clinician outcomes and support assessment of the feasibility, acceptability, and sustainability of the intervention.

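### The clinician-level model puts an unstructured covariance on 20 clinicians and takes its result at a final assessment that the article dates in three ways

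*Protocol article*

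**What the plan says.** The Statistical analysis section of the protocol article gives a single specification for both levels: "Analyses of differences in outcomes at both the patient- and clinician-level will include a linear mixed model to compare change in outcomes from baseline". The mean model is stated: "Fixed effects will include the study condition, assessment, study condition-by-assessment interaction, baseline measure, and any unbalanced covariates". So is the covariance: "Assessment will be treated as a categorical variable, and an unstructured variance–covariance structure will be used". An intervention effect is concluded if the arm-by-assessment contrast at the final assessment is significant, and "All tests of significance will be two-sided and a *p*-value of 0.05 will be considered statistically significant".

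On numbers, the Participants section says "A total of 20 clinicians (10 in each study arm) will be enrolled". The places that date the clinician assessments do not agree:

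- Abstract, Methods: "Quantitative and qualitative outcomes will be measured at 3- and 6-months post-baseline for clinicians". The last is 6 months.
- Study design: "Quantitative and qualitative outcomes will be measured at 3-, 6-, 9-,12-, 18-, 24-, and 30-months post-baseline for clinicians". The last is 30 months. The Quarterly survey section gives the same schedule.
- Researchers section, for practice-change data: "at the established intervals of 3-, 6-, 9-, 12-, 18-, and 30-months post baseline". The last is again 30 months, but 24 months is absent.
- Table 1: the clinician follow-up survey is marked at all seven of those times and again at close-out, at up to 37 months.

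**The concern.** Two things meet in the clinician-level analysis. First, the decision rule points to a final assessment that has three possible dates, so the article does not say which contrast decides the result. Left open, it could be settled after the data are seen. Second, a covariance that is comfortable for several hundred patients with four follow-ups is very rich for 20 clinicians with seven or eight. The article also foresees lost clinician data. Under Retention and withdrawal, clinicians on leave are not contacted, those who leave or change departments are withdrawn, and nothing new is collected after withdrawal. The last visit, which carries the verdict, is likely to have the fewest clinicians.

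The Objective section places clinician-level outcomes within the primary objective, and the Quarterly survey section uses clinician changes to help explain the patient results. A poorly determined or anti-conservative clinician test would affect both.

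**Working it through.** **The plan's own figure.** The article gives no power or error rate for clinician outcomes beyond the two-sided 0.05. Its patient-level figures reproduce. Effective n per arm = 300/(1 + 29 × 0.1) = 76.9. Power = Φ(d√(76.9/2) − 1.96), which is 79.7% at d = 0.45 and 87.3% at d = 0.5, against the stated 80.0% and 87%. Inflating for loss, 600/0.7 = 857.1, against about 856.

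**Parameter counts.** With T follow-ups, an unstructured covariance has T(T+1)/2 parameters. The mean model has 2T + 1 (two arms by T visits, plus baseline), before any unbalanced covariates.

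| Source | T | Last | Covariance | Mean | Most observations (20T) |
|---|---|---|---|---|---|
| Abstract | 2 | 6 months | 3 | 5 | 40 |
| Study design, Quarterly survey | 7 | 30 months | 28 | 15 | 140 |
| Researchers | 6 | 30 months | 21 | 13 | 120 |
| Table 1 | 8 | up to 37 months | 36 | 17 | 160 |

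**Error rate.** The stated model was simulated with no true effect: 10 clinicians per arm, arm by categorical visit plus baseline, unstructured covariance, REML. Assumptions not in the article: true correlation exchangeable 0.5 or AR(1) 0.8; 0-30% withdrawn by the last visit; 0-10% intermittent missing. Entries are the percentage of two-sided 5% tests that reject for the arm difference at the last visit. Near-singular means a smallest eigenvalue below 0.001.

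| T | Truth | Withdrawn / intermittent | z | Residual df | t, 17 df | Kenward-Roger | Near-singular |
|---|---|---|---|---|---|---|---|
| 2 | exch. | 0 / 0 | 6.7 | 5.9 | 5.3 | 4.2 | 0 |
| 7 | exch. | 0 / 0 | 7.4 | 7.2 | 5.3 | 6.5 | 0 |
| 7 | AR(1) | 0 / 0 | 7.2 | 6.9 | 5.6 | 6.8 | 0 |
| 7 | exch. | 10 / 0 | 7.3 | 7.1 | 5.4 | 5.5 | 0.1 |
| 7 | exch. | 20 / 0 | 7.9 | 7.5 | 6.7 | 4.7 | 0.1 |
| 7 | AR(1) | 20 / 0 | 9.7 | 9.2 | 7.0 | 4.7 | 0.2 |
| 7 | exch. | 30 / 0 | 9.9 | 9.6 | 7.7 | 6.2 | 1.3 |
| 7 | exch. | 10 / 10 | 9.5 | 9.1 | 7.7 | 6.6 | 25.1 |
| 8 | exch. | 0 / 0 | 6.3 | 6.1 | 4.7 | 5.3 | 0 |
| 8 | exch. | 20 / 10 | 10.8 | 10.8 | 9.3 | 5.9 | 71.5 |

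If the contrast is read instead as the last-visit difference minus the first-visit difference, the z figures in the two rows with intermittent gaps are 11.6% (T = 7) and 11.8% (T = 8). At T = 7 the model standard error is about 20% too small with 30% withdrawal, and about 17% too small with 10% withdrawal plus 10% intermittent missing.

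**Precision.** The z and t columns rest on 600 to 4,000 runs. At a true 5%, √(0.05 × 0.95/600) = 0.9 points and √(0.05 × 0.95/4000) = 0.3 points. Kenward-Roger used up to 600 runs. It could be computed in 486 of 600 in the seven-visit row with intermittent gaps, and in 118 of 300 in the eight-visit one, where the Monte Carlo error is √(0.05 × 0.95/118) = 2.0 points. A short run at T = 7 with 20% withdrawal plus 10% intermittent gave 8.8% on 80 usable fits (error 2.4 points), too few to separate from the rest. Some near-singular fits had not fully converged.

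**The case against.** A reader might infer that the plan, as written, doubles the false-positive rate. The documents do not support that. Doubling needs substantial missing clinician data and also a test without small-sample degrees of freedom. The article gives no clinician attrition rate. It describes pausing as pausing session participation and does not say that surveys stop, and practice-change data come partly from chart review. It names no degrees-of-freedom method, but that is commonly left to an analysis plan, which is not shown here. With complete data every seven-visit fit was estimable, and the error was about 7% even with z.

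A reader might also infer that compound symmetry should simply replace the unstructured matrix. That does not follow. With complete data, seven visits and Satterthwaite degrees of freedom, compound symmetry gave 5.1% error at the last visit when the truth was exchangeable. It gave 8.3% under AR(1) 0.8 per visit, and 11.8% under a correlation of 0.9 per quarter at the protocol's spacing (empirical SD 0.446 against a reported SE of 0.349). The simple structure can be worse at the very visit that decides. Moving the verdict to 12 months would be a preference and not a correction.

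The abstract may be loosely condensed, and the missing 24 months in the Researchers section does not move the last visit. Even so, the body text and the article's own schedule table disagree (30 months against close-out). That is a contradiction within the article, not a detail left to another document.

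**Conclusion.** The point holds in two parts. The dating conflict needs no simulation: the contrast that decides the clinician-level result could fall at 6 months, 30 months or a close-out of up to 37 months. The covariance problem is conditional. Without small-sample degrees of freedom, the error is about 7% with complete data, about 8-10% with 20-30% withdrawal, and about 9.5-12% once intermittent gaps are added. Kenward-Roger brings it to about 5-7% where the model can be fitted. Fitting then becomes the weak point: with intermittent gaps about 25% of seven-visit runs and about 70% of eight-visit runs were near-singular. These sizes rest on assumed correlations and attrition. If the abstract's two follow-ups were right, the covariance issue would largely vanish, so the schedule has to be settled first. The primary patient outcome, powered at 12 months, is not affected by the clinician dating conflict.

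**What to change.** For clinician outcomes only:

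1. Reconcile the abstract, Study design, Quarterly survey, Researchers and Table 1, and name one final clinician assessment for the decision before unblinding.
2. State REML with Kenward-Roger degrees of freedom.
3. Pre-state an ordered fallback if the unstructured fit fails or is near-singular. Begin with structures that allow decaying correlation and unequal variances (for example heterogeneous AR(1) or a spatial power structure for the uneven spacing), then compound symmetry. The decaying structures were not themselves simulated here.
4. Add a small-sample-corrected robust standard error as a sensitivity analysis.

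The cost is a few sentences and one decision on the date, with no new data. The downside is a simpler covariance assumption if the fallback is used. The plan already accepts one for clinicians: the GEE analysis of change in the intervention arm uses an exchangeable correlation.

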### Randomization, allocation concealment, and blinding

After eligibility and consent are confirmed and a baseline survey is completed, participating clinicians will be randomized at a ratio of 1:1 to one of the two study arms. An electronic randomization list will be generated using the latest version of the statistical software platform R (version 3.3.2, http://www.r-project.org). The list will be securely integrated into the cloud-based Research Electronic Data Capture (REDCap) tool. Allocation will be concealed from all investigators and staff until the study group is assigned. Only the study manager and research assistants involved in the delivery of the intervention components will subsequently be made aware of allocation. It is not possible to mask participating clinicians; however, their patients will have no knowledge of their potential participation in weekly teleECHO sessions, monthly interactive webinars, and quarterly short courses. All staff who are involved in the collection of data and investigators who conduct analyses will remain blinded to allocation throughout the study.

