### Sample size

To ensure that study has adequate power to determine the effectiveness of the intervention to improve outcomes of interest, we have powered our study on physical function after 12 months measured using the PROMIS-29. We believe that this will provide adequate power to examine differences in additional key outcomes (e.g., quality of life, anxiety, medication use, etc.) We calculated the sample size based on a two-sided, two-sample *t*-test at a significance level of 5%. The literature on minimally important differences in the PROMIS-29 domains suggests it is equal to 0.45–0.5 SD (4.5–5.0 points on a T-score metric). A 0.45–0.5 SD between group difference equates to a standardized effect size d between 0.45 and 0.5. As no similar cluster randomized controlled trial has been reported in the literature and Long COVID, ME/CFS, and other PIFI are heterogeneous, we have assumed that the intraclass correlation will be low (ICC = 0.1). Adjusting for this clustering of our primary outcome between 20 clinicians, we estimate that 600 patients (300 per condition, 30 per clinician cluster) will provide us with between 80.0% and 87% power. Assuming a loss to follow-up rate as high as 30% at the 12-month patient endpoint, we will aim to include approximately 856 patients (42 patients per clinician). In order to achieve balance in the proposed longitudinal cohort study, we will include 428 patients from the UW Medicine’s Post-COVID Telehealth Clinic.

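### The primary patient-level mixed model names no clinician term, although clinicians are randomised and the sample size assumes an ICC of 0.1 within clinicians

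*Protocol article*

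**What the plan says.** The unit of randomisation is the clinician. The section Randomization, allocation concealment, and blinding says that "participating clinicians will be randomized at a ratio of 1:1 to one of the two study arms", and the Participants section gives the number: "A total of 20 clinicians (10 in each study arm) will be enrolled".

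The Sample size section recognises the consequence. It states that "we have assumed that the intraclass correlation will be low (ICC = 0.1") and derives 600 analysed patients, 30 per clinician, with the words "Adjusting for this clustering of our primary outcome between 20 clinicians".

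The Statistical analysis section then sets out one linear mixed model for both patient-level and clinician-level outcomes:

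- Fixed effects: "Fixed effects will include the study condition, assessment, study condition-by-assessment interaction, baseline measure, and any unbalanced covariates".
- Covariance: "Assessment will be treated as a categorical variable, and an unstructured variance–covariance structure will be used".
- Success rule: the arm-by-assessment contrast at the final assessment, tested two-sided at 5%.

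Clinicians enter this description only as the basis for deciding which arm a patient belongs to. The exchangeable GEE later in the same section concerns changes over time among intervention-arm clinicians. It does not serve the randomised comparison of patient outcomes.

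**The concern.** An unstructured matrix over categorical assessments describes repeated measurements on one subject. For clinician-level outcomes the clinician is the subject, so the description is complete. For patient-level outcomes a level is missing: patients of the same clinician share that clinician's influence, and nothing named in the model absorbs it.

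The design step and the stated analysis therefore disagree. The sample size is inflated because patients within a clinician are correlated, while the model as stated would treat them as independent. Two things are at stake for the primary result. The standard error of the arm difference would be too small, and the reference distribution would rest on several hundred patients when the comparison is between 10 and 10 clinicians.

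**Working it through.** **Inputs, all from the Protocol article.** Two-sided 5% test; 20 clinicians, 10 per arm; 30 analysed patients per clinician, 300 per arm; ICC 0.1; standardised difference d = 0.45 to 0.5; stated power 80.0% to 87%.

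**Step 1: reproduce the stated power.**
- Design effect = 1 + (30 − 1) × 0.1 = 3.9.
- Effective patients per arm = 300 / 3.9 = 76.9.
- Standard error of the difference in SD units = √(2 / 76.9) = 0.161.
- Power = Φ(d / SE − 1.96), which is 79.7% at d = 0.45 and 87.3% at d = 0.5.

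This matches the article, so its sample size does use the design effect of 3.9, with a large-sample reference distribution.

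**Step 2: false-positive rate if no clinician term is fitted.** The model-based standard error is too small by the factor √(design effect), so the true two-sided error is 2Φ(−1.96 / √DE). This takes the ICC to apply to the quantity tested at 12 months.

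| ICC | Source | Design effect | True error of a nominal 5% test |
|---|---|---|---|
| 0.1 | stated in the article | 3.9 | 32.1% |
| 0.05 | assumed | 2.45 | 21.0% |
| 0.02 | assumed | 1.58 | 11.9% |

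Confidence intervals would have 1 / √3.9 = 0.51 of their proper width at ICC 0.1.

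**Step 3: check by simulation.** With 20,000 null trials of 20 clinicians × 30 patients at ICC 0.1, a patient-level t-test rejected in 32.4%. A t-test on clinician means rejected in 5.0%.

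**Step 4: sensitivity to the form of the test.**
- *Baseline adjustment.* The article gives no within-patient correlation. Assuming 0.6, a baseline-adjusted analysis (4,000 simulated trials) rejected in about 40% at ICC 0.1 and about 15% at ICC 0.02. Adjustment removed patient-level variance and left the clinician variance in place, so it does not cure the problem.
- *Contrast.* If the tested quantity were month 12 minus month 3 and clinician effects were constant over time, they would cancel and the error would stay near 5%. If clinician effects at the two visits correlated 0.8 or 0.5 (assumed), the error at ICC 0.1 would be about 21% or 34%.

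**Step 5: power with the correct reference distribution.** The between-clinician degrees of freedom are 20 − 2 = 18. With the design effect of 3.9 unchanged and a noncentral t distribution on 18 df, power is 75.2% at d = 0.45 and 83.4% at d = 0.5.

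**The case against.** The strongest reply is that the article is silent on random effects and does not exclude them. The quoted list covers fixed effects, where a clinician random effect would not appear. The method is called a linear mixed model, the trial is described as cluster-randomised, and the sample size allows for clustering. A full protocol exists and is not shown, and an analysis plan may exist too. An unstated clinician effect is therefore a plausible intention.

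That reply limits the claim. A reader might infer that the trial team means to ignore clustering, or that the primary result is bound to be invalid. The document supports neither. It supports only that no clinician term is named, and that the error rates above follow if the model is run as described.

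The reply does not remove the point. The section goes as far as the covariance structure, the missing-data assumption and the success rule, and what it leaves unstated is the level on which the sample size depends. The choice of degrees-of-freedom method or the reporting of the ICC could fairly wait for an analysis plan; whether the randomised unit is in the model is more basic.

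Two further limits stand. Only the figure of about 32% rests on stated inputs. A reader might take the lower rates as a range implied by the plan, but they need ICCs that the article does not give. The size also depends on the contrast: the arm difference in change at 12 months is the natural reading of the analysis and sample size sections together, but the literal month-12-versus-month-3 reading gives other values.

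**Conclusion.** The point holds in this form: as written, the primary patient-level model names no clinician term, in conflict with the unit of randomisation and with the article's own ICC of 0.1. Followed literally, it gives an invalid primary p-value and confidence interval.

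The false-positive rate is about 32% against a nominal 5%. This rests on ICC 0.1, 30 patients per clinician, no clinician level in the fitted model, and a test of the arm difference in change at 12 months. Smaller assumed ICCs reduce the inflation but do not remove it: about 21% at 0.05 and 12% at 0.02. Even if a clinician effect is intended, the degrees of freedom need stating, because the published power is reproduced only with a large-sample reference distribution.

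**What to change.** In the Statistical analysis section, state that for patient-level outcomes:

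- the model includes a random effect for clinician in addition to the unstructured within-patient covariance, or that an equivalent cluster-level analysis is used;
- inference uses a small-sample degrees-of-freedom correction for 20 clusters, giving about 18 df for the arm comparison;
- each patient stays in the cluster of the first-assigned clinician. This needs saying because the Retention and withdrawal section allows patients to move to another clinician in the same arm.

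The same sentence should say that the tested contrast is the arm difference in change from baseline to 12 months, if that is what is meant. Whether the clinician effect may also vary by assessment, and which degrees-of-freedom method is used, can be left to the analysis plan.

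The change needs no new data and does not affect trial conduct. Its cost is statistical: at ICC 0.1, intervals are about √3.9 = 1.97 times as wide as those from a model without the clinician term. The Sample size section should also restate power as about 75% (d = 0.45) to 83% (d = 0.5) in place of 80.0% to 87%.
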